### Study design

56 subjects will be randomized into 1 of 2 arms (Arm 1 and Arm 2) in a 1:1 ratio. These two arms will be double-blinded. Subjects in Arm 1 will receive JE-YF17D vaccine (IMOJEV^®^, Sanofi Pasteur) on Day 0, followed by YF17D vaccine (STAMARIL^®^, Sanofi Pasteur) on Day 28. Subjects in Arm 2 will receive YF17D vaccine on Day 0 followed by JE-YF17D vaccine on Day 28. A separate non-randomized non-blinded cohort of 14 subjects will be recruited into Arm 3. Subjects in Arm 3 will receive inactivated JEV vaccine (IXIARO^®^, Valneva) on Day 0 followed by YF17D vaccine on Day 28. **Table 1** summarizes the study design.

**Table 1 T1:** Study design.

Arms	Vaccination schedule	
	1^st^ vaccination (Day 0)	2^nd^ vaccination (Day 28)
Arm 1* (n=28)	JE-YF17D vaccine (IMOJEV^®^, Sanofi Pasteur)	YF17D vaccine (STAMARIL^®^, Sanofi Pasteur)
Arm 2* (n=28)	YF17D vaccine (STAMARIL^®^, Sanofi Pasteur)	JE-YF17D vaccine (IMOJEV^®^, Sanofi Pasteur)
Arm 3** (n=14)	Inactivated JEV vaccine (IXIARO^®^, Valneva)	YF17D vaccine (STAMARIL^®^, Sanofi Pasteur)

*Subjects (n=56) will be randomized in a double-blind manner to either Arms 1 or 2. **A separate cohort (n=14) will be recruited into Arm 3 in a non-randomized, single arm, open label design.

The rationale for these three study arms is as follows: Arm 1 will show the impact of a lower level of RNAemia induced by JE-YF17D vaccination (as compared to YF17D vaccination), and the resultant lower levels of virus-specific CD4+ and CD8+ T cells, would have on YF17D infection. In contrast, YF17D vaccination in Arm 2 would produce higher levels of RNAemia (as compared to JE-YF17D vaccination), and in turn higher levels of virus-specific T cells, thus likely resulting in greater suppression of JE-YF17D infection. The first vaccination in Arms 1 and 2 would provide the RNAemia response in the absence of virus-specific T cells, which would serve as a reference point to interpret the outcome of the second vaccination. For example, the level of suppression of JE-YF17D RNAemia will be the difference in RNAemia levels between subjects who received JE-YF17D as a second vaccination (Arm 2) compared to those who received it as a first vaccination (Arm 1), and similarly for YF17D vaccine. Arm 3 will serve as the control arm, as vaccination with inactivated JE vaccine should not produce any YF17D-specific T cell response.

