### Sample size calculation

To detect an effect size of 0.8 SD in mean RNAemia level on log (10) scale between the first and second dose with the same vaccine – first dose of YF17D will be analysed against those who received YF17D after JE-YF17D and vice versa – a sample size of 25 per group will provide 80% power at a 5% two-sided type 1 error rate. To allow for a drop-out rate of 10%, a total sample size of 28 per group for Arms 1 and 2 is targeted. For Arm 3, which is the control group, a sample size of 14 will be used.

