Linear regression analysis between peak RNAemia and T cell responses will performed to determine the minimal level of T-cell responses needed to reduce peak RNAemia by 1 log genome copies/ml. If, however, the correlation is non-linear (p > 0.05) a polynomial fit will be used to evaluate if a good model fit can be attained. Finally, in the unlikely event that none of these models fit the data points, the T-cell response for all subjects will be consolidated, and the T-cell responses that are at least 3 standard deviations away from the mean T-cell responses will be determined. These data points will be labelled as outlier responses, and the corresponding level of fold-change reduction in RNAemia will be determined. For all statistical comparisons, a p-value of <0.05 will be considered significant.

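### The threshold regression of peak RNAemia on T cells has no challenge-virus term or same-virus reference; if the arms are pooled, the virus difference alone tilts the slope towards the hypothesis

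*Protocol article*

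**What the plan says.** In the protocol article, Hypothesis and objectives names a minimum T-cell threshold for controlling a later infection as the study's overall goal. Data and statistical analysis gives the analysis that yields it: "Linear regression analysis between peak RNAemia and T cell responses will performed to determine the minimal level of T-cell responses" that brings peak RNAemia down by 1 log genome copies/ml. A polynomial follows if the linear fit fails. If that fails too, "the T-cell response for all subjects will be consolidated", and the RNAemia reduction in outlying T-cell responders is read off. No step mentions the challenge virus or the arm.

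Study design sets what each arm should bring to the challenge. On T cells, "YF17D vaccination in Arm 2 would produce higher levels of RNAemia (as compared to JE-YF17D vaccination"), and hence more virus-specific T cells; Arm 2 is then challenged with JE-YF17D. Arm 1 is expected to have fewer such T cells and is challenged with YF17D. Arm 3 should have no YF17D-specific T cells and is also challenged with YF17D.

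For suppression itself the protocol works within one virus. Study design takes the difference between subjects given a virus second and subjects given it first. Sample size calculation does the same: "first dose of YF17D will be analysed against those who received YF17D after JE-YF17D and vice versa".

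**The concern.** Peak RNAemia after challenge depends on which virus was given, and the protocol expects YF17D to give more than JE-YF17D. T-cell level and challenge virus are tied together by arm: high T cells go with the low-RNAemia virus, low or absent T cells with the high-RNAemia virus. A single line through all subjects credits the virus difference to T cells, in the direction the investigators expect. Measuring both viruses with one NS5 assay makes the values comparable but leaves this difference in place.

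The T-cell level said to buy 1 log of control could then partly reflect which vaccine each arm received second. The model also lacks a starting point for the reduction: a subject meets each virus only once, so 1 log lower has meaning only against a same-virus group reference, which the regression does not name.

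**Working it through.** **The plan's own figure.** "To detect an effect size of 0.8 SD in mean RNAemia level on log (10) scale" at 80% power and two-sided 5%: n = 2(1.960 + 0.842)² / 0.8² = 24.5, so 25 per group. Then 25 / 0.9 = 27.8, so 28. Both stated figures reproduce (the exact t-test gives 79.1% power at 25). They concern the same-vaccine contrast; the document gives no figure for the regression.

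**Inputs.** From the document: 25 evaluable in each of Arms 1 and 2; in Arm 3, 14 × 0.9, about 13; the arm-to-virus allocation; the direction of both gaps. Assumed, because not given: within-arm SD of 1 for T cells and for log10 peak RNAemia; T-cell gap *g* between Arms 1 and 2; gap *D* in RNAemia between the viruses (YF17D minus JE-YF17D); Arm 3's mean T-cell level; true T-cell effect of zero.

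**Expected pooled slope.** Let V = 1 for YF17D challenge and 0 for JE-YF17D. With no T-cell effect, slope = D × Cov(V,T) / Var(T).

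- Arms 1 and 2: slope = −D × (g/4) / (1 + g²/4). At g = 1: −D × 0.25/1.25 = −0.20 D.
- All three arms, T-cell means 1, 2 and 0 at g = 1: mean T = 75/63 = 1.190; Cov = 25/63 − (38/63)(1.190) = −0.321; Var = 1 + 0.567 = 1.567; slope = −0.205 D.

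Any D above zero gives a negative slope. At D = 0 the simulated error stays at about 5% two-sided.

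**How often it is significant.** Simulated trials with no T-cell effect; share with a significantly negative slope (nominal 2.5%). Set A puts Arm 3 1.5 SD below Arm 1 (4,000 runs); Set B puts it *g* below (2,000 runs).

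| g, D (SD) | Arms 1+2, A | Arms 1+2, B | All arms, A | All arms, B |
|---|---|---|---|---|
| 0.5, 0.5 | 6% | 7% | 11% | 8% |
| 1, 1 | 29% | 30% | 49% | 47% |
| 1, 1.5 | 50% | 48% | 77% | 73% |

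If first-dose observations were added at zero T cells (Set B, all arms, g = 1), the rate would be 20% at D = 1 and 32% at D = 1.5: lower, but still not nominal.

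**The false threshold.** If 1 SD of RNAemia equals 1 log (assumed), the median T-cell level read off as worth 1 log (Set B, all arms, g = 1) is 4.6 SD at D = 1, 3.2 at D = 1.5 and 2.4 at D = 2. The Arm 2 mean is 2, so the first lies largely beyond the data and the last well within them.

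**If T cells do work.** The same term adds to the true slope. With an illustrative true slope of −0.5 log per SD, the correct answer is 1/0.5 = 2.0 SD. Pooled at D = 1 and g = 1, all arms, it becomes 1/(0.5 + 0.205) = 1.4 SD, so the threshold is set too low.

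**With a virus term, or within YF17D-challenged subjects only.** The mean null slope is 0.00 (−0.005 to +0.007) and two-sided error is 4% to 6% in every Set B setting.

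**The case against.** The strongest objection is that pooling is inferred. The text never says that the first regression combines the arms. A reader might take "the T-cell response for all subjects will be consolidated" as proof, but that sentence belongs to the last fallback, and introducing consolidation only there could suggest that the earlier fits were separate. Elsewhere the protocol works virus by virus. The source is a condensed article, and an analysis plan not shown may stratify, which would remove the bias. This stands: pooling is the natural reading of one regression with no stratum, not a stated commitment.

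It also stands that the size is unknown. With both gaps at 0.5 SD and only Arms 1 and 2, the excess is 6% against 2.5%.

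A reader might go further and infer that the regression uses T cells drawn after challenge, or that undetectable peaks spoil it. The document supports neither. The regression sentence leaves the time point open, but the study goal concerns T cells present before infection and Table 2 includes a Day 28 pre-vaccination sample. No detection limit or undetectable fraction is given.

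The objection does not dispose of the point. The regression uses raw peak RNAemia where the rest of the protocol uses a same-virus difference. On the protocol's own premises, the pooled slope is biased towards the hypothesis.

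**Conclusion.** The point holds in conditional form. As written, the regression does not separate T-cell level from challenge virus; if arms are pooled, the virus difference alone pushes the slope negative and can yield a false 1-log threshold. The direction follows from Study design. The size, about 6% to 77% significantly negative null slopes against 2.5%, rests on assumed gaps of 0.5 to 1.5 SD, unit within-arm SDs and an assumed Arm 3 position.

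Two stronger conclusions are tempting and unsupported. One is that the design must produce a spurious threshold: a per-virus fit would prevent it, and small gaps give little bias. The other is that the trial's main comparison is compromised: the primary contrast is within the same vaccine, and "a sample size of 25 per group will provide 80% power at a 5% two-sided type 1 error rate" refers to that contrast. The regression is not among the listed primary or secondary objectives. It matters because it delivers the stated overall goal.

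**What to change.** State that the threshold regression, including its polynomial and outlier fallback steps, is fitted per challenge virus or with a challenge-virus term, checking that the T-cell slopes agree before quoting one threshold. Name the Day 28 pre-vaccination T-cell measure as predictor. Define the 1-log reduction against the same virus's first-dose mean: Arm 2 Day 0 vaccination for YF17D, Arm 1 Day 0 vaccination for JE-YF17D.

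Using reduction from that mean as the outcome also removes the bias, and with a virus term present it leaves the slope unchanged. Without the term, the reference's sampling error should be carried through: the difference between two means of 25 has SD √(1/25 + 1/25) = 0.28. Treating the references as known gave 5% to 9% two-sided error in simulations of the tabulated settings, with references drawn independently of the challenge data. The virus term is the simpler choice.

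The change needs a few lines of text and no new data. The price is precision. With all arms and both gaps at 1 SD (Set B), the average standard error of the slope rises from 0.11 to 0.12. For JE-YF17D alone the slope rests on variation within Arm 2: with about 25 subjects and unit SDs its standard error is about 1/√24 = 0.20, so a separate JE-YF17D threshold may be imprecise. For YF17D, Arms 1 and 3 both contribute, but Arm 3 is not randomised.

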## Hypothesis and objectives

The overall goal of this study is to define a minimum quantitative threshold of T cells induced by vaccination needed to control subsequent infection, independent of antibodies. We will conduct an experimental study in healthy adult volunteers, leveraging on the immunogenic properties of the licensed live-attenuated yellow fever (YF17D; STAMARIL^®^, Sanofi Pasteur) and chimeric Japanese encephalitis-YF17D (JE-YF17D; IMOJEV^®^, Sanofi Pasteur) vaccines. These vaccines contain the same genomic YF17D backbone (13, 14): vaccination with either vaccine would likely produce T cell responses that, like other flaviviruses, are preferentially directed against the non-structural proteins encoded in their shared genomic backbone, and hence would cross-protect against each other (**Figure 1**). YF17D and JE-YF17D, however, encode different structural pre-membrane (prM) and envelope (E) proteins: vaccination with either would produce neutralizing antibodies protective only against that virus (15). Moreover, YF17D and JE-YF17D vaccination induce different levels of infection as determined by vaccine RNAemia (16, 17), and expectedly differing levels of innate immune responses, allowing us to evaluate how RNAemia and innate immune profile shapes T cell response. The properties of these two live-attenuated vaccines thus provide a unique opportunity to differentiate the role of T cell immunity from humoral immunity in controlling viral infection. In addition, we will also use the licensed inactivated Japanese Encephalitis virus (JEV; IXIARO^®^, Valneva) vaccine to control for the effects of cross-reactive anti-flaviviral antibodies, although we have not observed suppression of YF17D RNAemia from inactivated JEV vaccination (16). Overall, we hypothesize that a high CD4+ and CD8+ T cell response will reduce RNAemia upon challenge with a structurally heterologous virus, and correspondingly result in reduced magnitude of host response to challenge infection. The specific objectives of the study are as follows:

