## Discussion

Although this study is focused on flaviviral vaccines, T cell immunity also plays a critical role in other viruses and viral vaccines. For example, although current COVID-19 mRNA vaccines are not able to sustainably protect against infection by the Omicron variant due to antibody escape mutations, protection against severe disease is maintained through preserved virus-specific T cell responses (23–28). We have also previously shown that the induction of T cell responses coincide with the onset of COVID-19 vaccine-induced protection, even prior to the appearance of neutralizing antibody responses (29). Thus, the findings from this trial would be applicable to many viral diseases.

The experimental medicine approach will enable the systematic study of the host T cell immune response to both vaccination and acute viral infection in a safe, controlled and ethical manner. In contrast, a “real world” study involving patients naturally infected with wild-type virus would be confounded by multiple factors, including virus strain variations and size of virus inoculum. As the exact timing of infection would be unknown, such studies would also encounter difficulty in obtaining pre- and post-infection samples at fixed time-points, and would require an unfeasibly large sample size in order to successfully test our hypotheses.

It can be argued that this study makes use of attenuated viruses, and thus the magnitude and quality of protective T cell responses measured would underestimate the threshold needed for immunity against wild-type virus as well as non-flaviviruses. Although this argument holds, our goal, however, is not to define a universal T cell correlate of protection. Rather, we submit that the use of attenuated viruses would establish a minimum threshold – the quantity and quality of T cell responses below such a threshold would unlikely be able to control any systemic wild-type viral infection. Such information would be foundational when selecting promising vaccine candidates for further clinical development.

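### The rule for the headline T-cell threshold has no outcome for a threshold that is not reached or not estimable, and at weak to moderate correlation it can return a very imprecise or too low value.

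*Protocol article*

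**What the plan says.** Under Hypothesis and objectives, the overall goal is to "define a minimum quantitative threshold of T cells induced by vaccination needed to control subsequent infection, independent of antibodies". Data and statistical analysis gives the method: a linear regression between peak RNAemia and T-cell responses "to determine the minimal level of T-cell responses needed to reduce peak RNAemia by 1 log genome copies/ml".

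The same paragraph fixes what follows. If the relation is judged non-linear, marked there by p > 0.05, "a polynomial fit will be used to evaluate if a good model fit can be attained". If neither model fits, an outcome the article regards as unlikely, subjects are combined and "the T-cell responses that are at least 3 standard deviations away from the mean T-cell responses will be determined"; the fold reduction in RNAemia at those outlying responses is then described.

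The paragraph does not say from which RNAemia level the 1 log is counted, or which arms enter the regression. Study design says that the first vaccination in Arms 1 and 2 gives RNAemia without virus-specific T cells, "which would serve as a reference point to interpret the outcome of the second vaccination". The Discussion then gives the result a lower-bound meaning: "responses below such a threshold would unlikely be able to control any systemic wild-type viral infection".

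**The concern.** A threshold read off a fitted line is a ratio with the slope in the denominator. When the slope is poorly determined, the ratio is much more so, and its interval may have no upper limit. A fitted line also returns a T-cell level for a 1-log fall even where few or no subjects were observed.

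The written sequence has three steps and none of them ends in a statement that no threshold could be established. The p-value also acts as a gate: linear thresholds come from slopes that happened to be significant, which at low power are on average too steep. A slope that is too steep gives a threshold that is too low.

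At stake is the study's main product. The Discussion treats T-cell responses below this level as unlikely to control wild-type infection and calls the information foundational for selecting vaccine candidates. A value that is too low, or that the data do not bound, would weaken that use.

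**Working it through.** **The plan's own figure.** Sample size calculation starts: "To detect an effect size of 0.8 SD in mean RNAemia level on log (10) scale between the first and second dose". With 80% power and two-sided 5%, n = 2(1.960 + 0.842)²/0.8² = 24.5, so 25 per group; exact t-test power at 25 is 0.79. Allowing 10% drop-out, 25/0.9 = 27.8, so 28. The figures reproduce. They concern a difference in means; the precision of the threshold is not part of this calculation.

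**Inputs for the threshold.**
- n = 25: one randomised arm, evaluable subjects (Sample size calculation). n = 50: Arms 1 and 2 pooled.
- r, the correlation of peak log10 RNAemia with T-cell response: not in the documents; assumed 0.3 to 0.8.
- SD of peak log10 RNAemia: not in the documents; assumed 0.6 or 1.0 where needed.
- The p-value in the rule is read as that of the linear term.

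**Interval.** Take the threshold as 1/|slope|. With t = r√(n−2)/√(1−r²) and c the 97.5% t quantile on n−2 degrees of freedom (2.069 at n=25, 2.011 at n=50), the 95% Fieller limits are the estimate times 1/(1+c/t) and 1/(1−c/t). If t < c there is no upper limit.

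Example, n=25 and r=0.5: t = 0.5 × 4.796/0.866 = 2.769; c/t = 0.747; limits 1/1.747 = 0.57 and 1/0.253 = 3.95.

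| r | n=25 | n=50 |
|---|---|---|
| 0.3 | no upper limit | 0.52 to 13 |
| 0.4 | 0.50 to 86 | 0.60 to 2.98 |
| 0.5 | 0.57 to 3.95 | 0.67 to 2.01 |
| 0.6 | 0.63 to 2.35 | 0.72 to 1.63 |
| 0.7 | 0.69 to 1.79 | 0.77 to 1.42 |
| 0.8 | 0.76 to 1.48 | 0.82 to 1.28 |

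The table treats r as the observed correlation. If r=0.5 is the true value, samples vary around it: at n=25 about 26% (normal T-cell distribution) to 36% (log-normal) of simulated trials had no upper limit.

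**Position.** The slope is r·SD(RNAemia)/SD(T cell), so a 1-log fall needs 1/(r·SD) standard deviations of the T-cell measure above zero. With r=0.5 and SD 0.6 that is 1/0.30 = 3.3. At n=25 the estimated threshold then lay beyond at least 95% of subjects in 44% (normal, mean 2 SD above zero) to 68% (log-normal) of simulated trials. With r=0.7 and SD 1.0 this happened in 1% to 9%.

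**Selection by p < 0.05.** In 20,000 simulated regressions per setting, these are the medians of estimated over true threshold among significant slopes:

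| r | n=25 | n=50 |
|---|---|---|
| 0.3 | 0.61 | 0.80 |
| 0.4 | 0.78 | 0.94 |
| 0.5 | 0.90 | 0.99 |
| 0.6 | 0.97 | 1.00 |
| 0.7 | 1.00 | 1.00 |

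This models the linear step only. The polynomial fallback is not simulated.

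**The case against.** The strongest reply is that much of this is silence in a condensed journal article. A reader might infer that the trial intends to publish a bare number without an interval. The article does not say so, and an analysis plan that is not shown may supply the interval. That part of the reply stands, so the missing interval is not the finding on its own. The article does, however, spell out a sequence with two fallbacks, and that sequence has no exit for a threshold that cannot be established.

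A reader might also infer that sizing for 0.8 SD contradicts a 1-log target. It does not. The first is a detectable difference between group means and the second is a point on a regression curve. They are different quantities and need not agree.

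Nor does the plan report a threshold only when p < 0.05. Above that it turns to a polynomial, which may also yield one. The selection figures therefore describe the linear thresholds and not the whole procedure.

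One over the slope is one reading. Counted from the first-dose reference in Study design, the threshold becomes an inverse prediction that also involves the intercept, still with the slope as denominator. The polynomial and outlier steps are not of this form.

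Pooling matters too. Adding about 13 Arm 3 subjects at zero T-cell response narrows the n=25, r=0.5 interval from about 7-fold to about 2.7-fold (normal) or 4.7-fold (log-normal).

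Finally, the Discussion disclaims a universal correlate of protection and sets no operational cut-off, so the number is not a formal selection rule.

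**Conclusion.** The point holds in limited form. The written rule for the study's overall goal can return a threshold that the data do not bound or that lies beyond nearly all subjects, and it provides no way to say so. The linear step can also give a value that is too low.

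The size depends on r, the SD of peak RNAemia and the pooling of arms, none of which the article states. With one arm of 25 the problem is serious at r of about 0.4 and material at 0.5 (a 6.9-fold interval). By r=0.7 the interval is 2.6-fold with essentially no selection bias. With 50 pooled, the interval is 5.0-fold at r=0.4, 3.0-fold at r=0.5 and 1.8-fold at r=0.7. The documents do not show which of these settings applies. That is a reason to write the rule so that it works in all of them. The change is worth making before analysis; confidence is medium.

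**What to change.** In Data and statistical analysis:

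1. Report the threshold with a 95% Fieller or bootstrap interval, whatever the p-value of the linear term.
2. If the point estimate lies outside the observed pre-challenge T-cell range, or the interval is unbounded, report the threshold as not reached or not precisely estimable. In that case give the estimated suppression of peak RNAemia, with 95% confidence intervals, at the observed quartiles of T-cell response.
3. Do not require the upper confidence limit to lie inside the observed range. That is too strict: with log-normal T-cell responses (CV 0.7), SD 1.0 log and r=0.5, all assumed, a true threshold at 1.4 times the mean response would pass in only 30% of simulated trials at n=25 and 56% at n=50.

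Stating the reference level for the 1 log and the arms included would make the estimate reproducible.

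The cost is plan wording and a few lines of code; visits, procedures and sample size do not change. The downside is that the trial may have to report a wide interval, or that no threshold was established.

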#### Vaccine RNAemia

Vaccine RNAemia (as well as urine viral RNA levels) will be measured using RT-qPCR directed against the NS5 gene of YF17D, allowing RNAemia levels induced by JE-YF17D vaccination and YF17D vaccination to be directly compared.

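### The T-cell threshold comes from ordinary regression with no provision for peak RNAemia below the RT-qPCR detection limit, so it can be biased in either direction, with the JE-YF17D challenge most exposed

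*Protocol article*

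**What the plan says.** Under Hypothesis and objectives, the protocol article makes a minimum T-cell threshold the overall goal of the study. Data and statistical analysis fixes how it is obtained: "Linear regression analysis between peak RNAemia and T cell responses will performed", in order to "determine the minimal level of T-cell responses needed to reduce peak RNAemia by 1 log genome copies/ml". If the relation is not linear, "a polynomial fit will be used to evaluate if a good model fit can be attained". If neither model fits, a rule based on responses 3 standard deviations from the mean takes over.

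The section on vaccine RNAemia says that RNAemia "will be measured using RT-qPCR directed against the NS5 gene of YF17D", with one assay for both live vaccines. The sample size section places RNAemia on the log10 scale: "To detect an effect size of 0.8 SD in mean RNAemia level on log (10) scale".

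Study design states that JE-YF17D produces less RNAemia than YF17D ("Arm 1 will show the impact of a lower level of RNAemia induced by JE-YF17D vaccination (as compared to YF17D vaccination"). For Arm 2, primed with YF17D and challenged with JE-YF17D, it expects higher T-cell levels, "thus likely resulting in greater suppression of JE-YF17D infection". It defines suppression as a difference between groups: the same vaccine given second in one arm against first in the other.

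The article gives no detection limit, no expected RNAemia level, and no statement of how an undetectable peak enters the regression.

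**The concern.** An RT-qPCR result has a lower detection limit, and an undetectable sample has no log10 value. For such a peak one knows only that it lies below the limit: it is left-censored. Ordinary linear or polynomial regression needs a number, so the analyst must substitute one or drop the subject.

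That would matter little if undetectable peaks were spread evenly over T-cell response. The design's own rationale predicts otherwise. The strongest suppression is expected on the virus that starts lower, so subjects with high T-cell responses are the likeliest to fall below the limit. Censoring then depends on the predictor and changes the slope. The polynomial fallback does not help, because it would fit the flattening at the floor as if it were biology.

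The slope determines the threshold, which the Discussion wants to use in selecting vaccine candidates. A threshold set too high could reject an adequate candidate; one set too low could pass an inadequate one.

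**Working it through.** **The plan's own figure.** The only reproducible figure is the sample size. n per group = 2(1.960 + 0.842)²/0.8² = 24.5, so 25; allowing 10% drop-out, 25/0.9 = 27.8, so 28. Both agree with the protocol, and this point does not touch them.

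**Inputs for the bias check.** All are assumptions, because the documents supply none:
- log10 peak above the detection limit = μ − 0.5·T + error, where μ is the mean unprimed peak above the limit;
- T-cell response T normal, mean 1.5, SD 0.75 (arbitrary units);
- residual SD 0.6, varied from 0.4 to 0.8.

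The true T-cell difference for a 1-log fall is 1/0.5 = 2.0 units.

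**Formula.** The primed peak has mean m = μ − 0.75 and SD s = √(0.375² + 0.6²) = 0.7075. Let P = Φ(m/s) be the detectable share and f = φ(m/s)/s the density at the limit. If undetectable peaks are coded d log below the limit, then with normal T and normal errors (Stein's lemma) the large-sample ordinary slope is −0.5·(P + d·f). Hence

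threshold = 2.0/(P + d·f),

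with d = 0 for coding at the limit, 0.301 for half the limit, and 2 for coding as 1 copy when the limit is 2 log.

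**Example, μ = 1.0.** m = 0.25, P = 0.638, f = 0.530.
- At the limit: 2.0/0.638 = 3.13.
- Half the limit: 2.0/(0.638 + 0.301 × 0.530) = 2.51.
- 1 copy: 2.0/(0.638 + 2 × 0.530) = 1.18.

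**Results** (truth 2.0). The first three threshold columns come from the formula; the last two are simulated with 25 subjects.

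| μ (log above limit) | Undetectable | At limit | Half limit | 1 copy | Dropped | Tobit |
|---|---|---|---|---|---|---|
| 3 | 0% | 2.00 | 2.00 | 1.99 | 1.99 | 1.99 |
| 2 | 4% | 2.08 | 2.01 | 1.67 | 2.22 | 1.97 |
| 1.5 | 14% | 2.34 | 2.10 | 1.33 | 2.72 | 2.01 |
| 1.0 | 36% | 3.13 | 2.51 | 1.18 | 3.94 | 2.03 |
| 0.5 | 64% | 5.53 | 3.84 | 1.41 | 5.68 | 2.01 |

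Large-sample simulation of the three coding rules agrees with the formula to within 0.04. Over all peak levels simulated, from 0.5 to 4 log, Tobit ranges from 1.94 to 2.03.

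**Sensitivity.**
- Residual SD from 0.4 to 0.8 moves the at-limit result at μ = 1.0 only from 2.96 to about 3.3.
- Reading the fall against the mean of a first-dose group, as Study design describes suppression, keeps the pattern: in simulation at μ = 1.0, 2.80 at the limit and 1.25 for 1 copy.
- Coding as 1 copy understates the threshold when d·f exceeds the undetectable share, 1 − P. This can fail: with a limit of 1 log (d = 1) and μ = 0.5, the result is 2.0/(0.362 + 0.530) = 2.24, an overestimate.
- Half-limit coding is practically unbiased when few peaks are undetectable.

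**The case against.** The strongest reply is that the article is silent rather than wrong. Rules for results below a detection limit are commonly left to an analysis plan or full protocol, and neither is shown. That stands for the substitution rule, and its absence is not the point here. The model class is different: the article itself chose ordinary linear regression with a polynomial fallback and a fixed 1-log target, and no substitution rule makes those models handle censored values properly.

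A reader might infer that the 1-log fall is a responder criterion under which fully suppressed subjects are scored too low. The documents do not support that. The 1 log is read off a fitted line, and no subject is classified. In Arms 1 and 2 each subject receives each live virus once, so no individual unprimed peak exists for the challenge virus.

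A reader might also infer that the threshold is bound to be overestimated. That does not follow either: coding undetectable peaks as 1 copy usually reverses the sign.

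It is also fair that every magnitude is assumed. Study design says only that JE-YF17D RNAemia is the lower of the two, not that it lies near the limit. Tobit was tested on data that meet its normal-residual assumption, so its performance above is a best case. Finally, the plan already allows a Wilcoxon rank-sum test for peak and AUC comparisons, so those need no repair.

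**Conclusion.** The concern holds in conditional form. The analysis that delivers the study's main goal makes no provision for left-censored peaks, although the design makes them foreseeable at high T-cell values, above all for the JE-YF17D challenge. If they occur in number, the threshold depends on how they are coded. At an unprimed mean 1 log above the limit it runs from 1.18 (1 copy) to 3.94 (dropped) against a truth of 2.0, a 3.3-fold spread (3.94/1.18).

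The direction is upward for substitution at the limit or half the limit or for dropping, and generally downward for 1 copy. Under the assumed inputs the bias is negligible at about 3 log above the limit. At 2 log it is small for substitution at or near the limit (2.08), though 1-copy coding already gives 1.67. At 1 log or less it is substantial. Which case applies to this trial cannot be told from the documents. Only the relative exposure of the two challenges follows from them, in direction and not in size.

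**What to change.** In Data and statistical analysis, replace the ordinary threshold regression with a left-censored (Tobit) regression of log10 peak RNAemia on T-cell response. Censor at the detection limit of the NS5 assay, state that limit, and fit the model separately for each challenge virus. Report the proportion with undetectable RNAemia alongside each fit. Give ordinary regression, with its coding of undetectable peaks stated, as a sensitivity analysis. A separate success criterion for the lower-RNAemia virus is unnecessary once the model handles censoring.

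The cost is a change of analysis wording, with no new samples or subjects. The model relies on normal residuals, which should be checked, and its intervals will be slightly wider. The group comparisons of peak and AUC and the sample size stay as they are.
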